### Approval

This study follows the Dutch Medical Research Involving Human Subjects Act's (WMO) and the Helsinki Declaration's principles, meaning that the (legal) representatives of all demented patients will sign a written informed consent, stating also that participation can be withdrawn at any time, whenever the patient shows resistance, without any negative consequences concerning their current or future medical treatment. The Medical Ethical Committee of Maastricht University has granted ethical approval (protocol 2011 nr. NL35287.068.11).

### Statistical analysis

In order to process the data to test our hypothesis, the statistical software programme SPSS-19 [34] will be used. First, data will be checked for missing values and normal distribution. It will be examined whether there is a significant difference in both nocturnal restlessness and degree of neuropsychiatric symptoms between the intervention group and the control group.

To analyze the actigraphy variables and the variables measured by means of NPI-NH (T0, T1, and T2) integrally, a multilevel regression model (Mixed Models) will be used. In this study, the Basic Two-Level Regression Model [35] will be used, in which the actigraphy variables and NPI-NH variables are the lowest levels (that is dependent variable) and the research participants the highest level (independent variable).

The multilevel analysis enables us to calculate the degree of nocturnal restlessness and neuropsychiatric symptoms despite the unequal number of observations per individual (missing values/dropouts). This means that all data will be included in the analysis, including the data of participants who will meet stop criteria during the investigation and for whom the study has to be terminated early.

If there is interaction effect between time and group, a post-hoc analysis will be performed, taking into account that T0-T1 indicates PAS therapy effects and that T1-T2 indicates the long-term effects of PAS therapy. The analyses will be corrected for basic differences in the characteristics of the patients belonging to the intervention group and the control group respectively. The data in the sleep diaries will first be coded and later analyzed separately by means of describing statistics.

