### Procedure

After including the patients for participation in the study, they will be divided into an intervention and control group by means of randomization. We have not opted for a crossover design, as it cannot be estimated how long the wash-out period will be [19]. For the sake of the validity of the results to be obtained, a period of six weeks (2 + 2 + 2) has been chosen for the intervention group as well as for the control group. During this total period, both groups of demented patients will continuously wear an actiwatch (respironics type AW2) on the non-dominant wrist. Practice has shown that this watch hardly causes any nuisance or no nuisance at all.

In addition, a daily sleep diary will be kept by the nursing staff for all participants.

In the first two weeks, the baseline situation (T0) of the intervention group and control group will be measured by means of the actiwatch. In the next two weeks, as the intervention is executed in the intervention group, in both groups the actiwatch measurements will be continued (T1). In the last two weeks the wash-out of the intervention will be measured and again in both groups the actiwatch measurements will be continued (T2).

During the whole period, the doors of the bedrooms of all participants in both groups will remain closed during the night, in order to prevent disruptions. Yet, if a patient or staff member enters/leaves the room, this will be noted in the sleep diary.

After the study period of six weeks, the actiwatches will be read out. The collected data per patient will be recorded, together with the other relevant data. These include registered changes in the situation of the patients during the study period, for example (1) possible additional co-morbid illness(es) that may lead to a change in the level of motor restlessness or in the normal day/night pattern of the patient (for example pneumonia, delirium, urinary retention, constipation), or (2) changes in the use of psychotropic drugs, therapies, and/or use of restraints.

A schematic representation of the procedure can be found in Table 1.

**Table 1 T1:** Measurements overview

Moment	T0	Baseline	T1	Baseline	T2	Intervention	T3	Intervention	T4	Wash-out	T5	Wash-out	T6
Week	0	1		2		3		4		5		6	
Actiwatch		Continuous		Continuous	*Charging*	Continuous		Continuous	*Charging*	Continuous		Continuous	
NPI-Q					T2				T4				T6
BANS-S	T0												
Patient characteristics	T0												

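### The T1-T2 contrast is labelled the long-term effect of PAS, but it measures loss of effect after stopping; persistence is the T0-T2 contrast, which the plan does not name

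*Protocol article*

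**What the plan says.** The Procedure section defines three two-week periods. For T0: "In the first two weeks, the baseline situation (T0) of the intervention group and control group will be measured". T1 is the following two weeks, when the intervention group receives PAS and both groups are still measured. For T2: "In the last two weeks the wash-out of the intervention will be measured". The Interventions section confirms that in this third period the intervention patients are back in their own beds.

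The Statistical analysis section puts all three periods into one model, for actigraphy as well as for neuropsychiatric symptoms: "variables measured by means of NPI-NH (T0, T1, and T2) integrally, a multilevel regression model (Mixed Models) will be used". It makes the follow-up comparisons conditional: "If there is interaction effect between time and group, a post-hoc analysis will be performed". The meaning of the two contrasts in that step is then fixed by one clause: "taking into account that T0-T1 indicates PAS therapy effects and that T1-T2 indicates the long-term effects of PAS therapy". No T0-T2 contrast and no group comparison at T2 is given a meaning. The Primary outcome measures section refers to the difference across T0, T1 and T2 without choosing a contrast.

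Table 1 uses T0 to T6 for weekly moments. The labels here are the period labels of the Procedure text, the only ones under which the analysis paragraph makes sense.

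**The concern.** A long-term or lasting effect is a benefit still present after treatment stops. It is judged against where the patient started and against the control group. T1-T2 instead compares the treated period with the untreated one that follows. In the PAS arm it shows a change if the benefit fades and no change if the benefit holds. The label therefore points the wrong way.

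The contrast is also ambiguous taken alone, because a value of zero fits both full persistence and no effect at any time. An analyst who follows the stated interpretation could describe a return of restlessness as a long-term effect of PAS, or conclude from a flat T1-T2 that there is none when the benefit has been kept. Persistence matters in this trial: one third of the measurement time is spent on wash-out, and a crossover was rejected because the length of wash-out could not be estimated.

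**Working it through.** **Inputs.** The plan gives no figure for either contrast, so there is none to reproduce. The Sample size section supplies a control frequency of 80%, assumed stable, and an expected PAS frequency of 50%, which is 30 points lower. I assume the PAS arm also starts at 80%. The level at T2 is not given, so I show the range from full persistence to full loss.

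**Formula.** For periods a and b, the group contrast is (PAS at b − PAS at a) − (control at b − control at a). With control at 80% throughout, the second bracket is 0. If a fraction p of the benefit remains at T2, the PAS level there is 80 − 30p. Then:

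- T0-T1 = 50 − 80 = −30
- T1-T2 = (80 − 30p) − 50 = 30(1 − p)
- T0-T2 = (80 − 30p) − 80 = −30p

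**Results in percentage points.**

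| Situation | PAS at T0, T1, T2 | T0-T1 | T1-T2 | T0-T2 |
|---|---|---|---|---|
| Benefit fully kept (p = 1) | 80, 50, 50 | −30 | 0 | −30 |
| Half kept (p = 0.5) | 80, 50, 65 | −30 | +15 | −15 |
| Benefit gone (p = 0) | 80, 50, 80 | −30 | +30 | 0 |
| Never any effect | 80, 80, 80 | 0 | 0 | 0 |

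Over this range T1-T2 grows as persistence shrinks, while T0-T2 tracks persistence. No standard deviation or correlation is needed.

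**Chance of a significant result (illustrative).** Assume compound symmetry, categorical time, two-sided 5% tests and 80% power for T0-T1 tested alone. None of this comes from the documents. The noncentrality of T0-T1 is then 1.96 + 0.84 = 2.80.

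| Benefit kept | T1-T2 significant | T0-T2 significant |
|---|---|---|
| Fully | 5% | 80% |
| Half | 29% | 29% |
| None | 80% | 5% |

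With these equal-variance assumptions the mirror image follows by construction. It illustrates the table of contrasts and is not separate evidence.

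**The interaction step, same assumptions.** The 2-df time-by-group test has power 83%, 71% and 83% for benefit fully, half and not kept. The chance that both it and T0-T1 are significant is 76%, 70% and 76%, against 80% for T0-T1 alone. The cost is 80 − 76 = 4 to 80 − 70 = 10 points. Splitting alpha over two contrasts by Bonferroni (critical value about 2.24) gives T0-T1 power of Φ(2.80 − 2.24) = Φ(0.56), about 71%.

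**The case against.** The best defence is that the two contrasts are meant to be read together. Improvement followed by no change suggests maintenance, improvement followed by worsening shows loss, and the sign of T1-T2 separates the two. The authors plainly know that treatment has stopped, since they call the period wash-out. T0-T2 is the sum of the two named contrasts and can be taken from the same model. An article may also leave a full contrast list to another document.

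Part of this stands. The plan does not say that a significant T1-T2 will be reported as lasting benefit. A reader might infer that it commits to that error, but the text only assigns the contrast a wrong meaning and so leaves the error open. The joint reading does not repair it, because it would take a non-significant T1-T2 as proof of persistence when it is only absence of evidence of loss. Nor is this a detail deferred elsewhere: the article states a specific interpretation, and that interpretation is wrong.

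A second stronger reading is that the main hypothesis has been demoted, because T0-T1 is tested post hoc and only after a significant interaction. The general sentence "It will be examined whether there is a significant difference in both nocturnal restlessness and degree of neuropsychiatric symptoms" names no period, so it supplies no direct T0-T1 test. Even so, the documents do not support calling this an error. The primary outcome spans all three periods, and a three-period interaction is a matching test of it. Both follow-up contrasts are named in advance, so post hoc here means follow-up and not data-driven. The sequence is conventional, does not inflate error and gives some protection across two contrasts. Its 70% to 76% joint power is comparable with the roughly 71% under Bonferroni.

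**Conclusion.** The interpretation of T1-T2 is wrong under the plan's own period definitions and needs correcting. Between full persistence and full loss, the contrast runs from 0 to 30 points in the direction opposite to persistence, and it cannot tell full persistence from no effect. This rests only on the protocol's 80% and 50% figures, a stable control group and equal starting levels.

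It should not be stretched to say that T1-T2 is always largest when the benefit disappears. Restlessness rising above baseline after stopping, or further improvement in wash-out, could also produce a large value. The reading of T0-T1 as the therapy effect is correct and unaffected. The term long-term is also too strong for observation that ends two weeks after withdrawal. The 4 to 10 points of power lost to the interaction step depend on assumptions outside the documents and are a matter of preference.

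**What to change.** Revise the interpretation in the Statistical analysis section as follows:

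- Define persistence as the between-group contrast from T0 to T2, or equivalently in purpose as the group difference at T2 adjusted for T0.
- Call it the effect remaining up to two weeks after stopping, and drop the term long-term.
- Report T1-T2 only as loss of effect after withdrawal, with its sign and confidence interval, and do not read a non-significant result as persistence.

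The cost is wording and one more named contrast from the same mixed model; data, visits and sample size do not change.

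Optionally, name T0-T1 as the single primary contrast and test it directly. This would recover the 4 to 10 points under the assumptions above, but it means choosing one primary contrast where the plan now has an outcome across three periods.

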### Randomization

By means of blinded block randomization with group sizes of six, the randomization scheme will determine which patients will be placed in the intervention group and the control group. The intervention is not blinded because it is visible for the caregiver (box with computer below the bed and faintly audible (a very low buzz).

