### Data collection

First, the following patient characteristics will be collected for both groups: age, gender, type of dementia, co-morbidity (by means of CIRS [20]), incontinence Yes or No, the use of restraints (for example fixation belts), medication (including psychopharmacological drugs), and other therapies.

In addition, the Bedford Alzheimer Nursing Severity Scale (BANS-S) [21] will be applied by the psychologist together with the nursing staff to get an impression of the severity of dementia. This validated scale contains seven items to assess functional and cognitive capacities as well as pathological symptoms. These items, scaled 1 to 4, are summed. The overall score ranges from 7 (no impairment) to 28 (complete impairment).

Although the traditional 'gold standard' assessing the quality of the sleep is polysomnography (PSG), it is difficult to apply PSG to patients with a moderate to serious form of dementia [22,23]. Therefore, in studies like this, often more feasible assessment methods are used, like observation-oriented techniques and actigraphy. Actigraphy is a less invasive method than PSG, offering a reliable way to estimate sleep/wake parameters including nocturnal restlessness [24]. In this study we will use both actigraphy and sleep diaries.

The nocturnal restlessness will be measured by validated actigraphy [25-27] in the intervention group as well as in the control group on the basis of the following sleep/wake parameters [28,29]: (1) nocturnal restlessness: average motor activity during the night; (2) sleep efficiency: the number of hours the patient is lying in bed and actually sleeping; (3) wake bouts: the number of episodes the patient is awake during the night; (4) inter-daily stability: the degree of stability in activity patterns over longer periods of time; (5) intra-daily variability: the degree of inconstancy in rest and activity during a day [28,29].

When considering nocturnal restlessness it is important to take measurements during a period of at least two weeks. In this way, the statistic power will increase [30].

To determine the degree to which the actimeters respond to the acoustic vibrations of the mattress themselves, a control actimeter is placed on the mattress in advance.

In addition, other relevant sleep observation data of every patient will be written down in a sleep diary, in which nocturnal restlessness and the day/night rhythm, as observed by the nursing staff will be recorded.

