### Primary outcome measures

The objectively and subjectively measured difference in nocturnal restlessness between T0-T1-T2. Objectively, the nocturnal restlessness measured during six weeks by means of an actiwatch validated for sleep research with the sleep/wake parameters mentioned above.

Subjectively, nocturnal restlessness determined on the basis of a sleep diary developed for this study, and filled in by the nursing staff.

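### The PAS effect is estimated as a comparison of T0-T1 changes, and covariates are picked from arm differences; using T0 as a baseline and naming covariates in advance would gain precision at no cost

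*Protocol article*

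**What the plan says.** All statements are in the protocol article. T0 here means the two-week baseline period described under Procedure, not the moment labelled T0 in Table 1.

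- **Model.** Under Statistical analysis: "To analyze the actigraphy variables and the variables measured by means of NPI-NH (T0, T1, and T2) integrally, a multilevel regression model" is to be used, "in which the actigraphy variables and NPI-NH variables are the lowest levels (that is dependent variable". T0 is therefore one of the outcomes.
- **Effect.** If time and group interact, a post-hoc analysis follows in which "T0-T1 indicates PAS therapy effects and that T1-T2 indicates the long-term effects of PAS therapy".
- **Primary outcome.** Under Primary outcome measures: "The objectively and subjectively measured difference in nocturnal restlessness between T0-T1-T2".
- **Covariates.** Under Statistical analysis: "The analyses will be corrected for basic differences in the characteristics of the patients belonging to the intervention group and the control group respectively". No covariate is named. Data collection lists the patient characteristics, starting with "age, gender, type of dementia, co-morbidity (by means of CIRS [20]), incontinence Yes or No, the use of restraints" and continuing with medication and other therapies; BANS-S is recorded in addition. The actigraphy value at T0 is not among them.
- **Baseline and allocation.** Under Procedure: "In the first two weeks, the baseline situation (T0) of the intervention group and control group will be measured by means of the actiwatch". Under Randomization: "By means of blinded block randomization with group sizes of six".

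**The concern.** Two choices in one section deserve a second look.

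First, each patient contributes two weeks of actigraphy before any treatment, yet T0 enters only as one end of a change. In a randomised trial the arms share the same expected T0 value. A model that estimates a separate T0 mean in each arm does not use that fact and pays for it in precision.

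Second, the trigger for covariate adjustment is a difference between the arms (I read the article's 'basic' as 'baseline'). Under correct randomisation such differences are chance. The rule therefore picks covariates by imbalance rather than by how well they predict restlessness, and the set cannot be known before the data are seen.

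At stake are the width of the confidence interval for the PAS effect and whether the adjusted model is fixed in advance.

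**Working it through.** **Inputs.** The article gives no standard deviation and no T0-T1 correlation, so it has no figure of its own to reproduce for this contrast. I assume equal variances at T0 and T1, complete data, and rho from 0.3 to 0.9. Sample size gives 33 per arm with 10% drop-out: 33 x 0.90 = 29.7, about 30 evaluable per arm (60 in all).

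**Variance per patient, in units of SD squared.**

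- Change from T0 to T1: 2(1 - rho)
- T1 adjusted for T0: 1 - rho^2
- Ratio, adjusted to change: (1 - rho)(1 + rho) / [2(1 - rho)] = (1 + rho)/2

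**Power.** Take an effect with 80% power under the change contrast at two-sided 5%. Its power after adjustment is Phi[(1.960 + 0.842)/sqrt(ratio) - 1.960]. At rho 0.7: 2.802/sqrt(0.85) - 1.960 = 1.079, so 86%.

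| Assumed rho | Change | Adjusted | Ratio | Patients needed to match 60 under change | Power (80% under change) |
|---|---|---|---|---|---|
| 0.3 | 1.40 | 0.91 | 0.65 | 39 | 93.5% |
| 0.5 | 1.00 | 0.75 | 0.75 | 45 | 90% |
| 0.6 | 0.80 | 0.64 | 0.80 | 48 | 88% |
| 0.7 | 0.60 | 0.51 | 0.85 | 51 | 86% |
| 0.8 | 0.40 | 0.36 | 0.90 | 54 | 84% |
| 0.9 | 0.20 | 0.19 | 0.95 | 57 | 82% |

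**Simulation.** 30 per arm, 8,000 runs with no treatment effect, five independent candidate covariates of which one is prognostic. Imbalance was defined as p < 0.05, an illustrative cut-off because the article states none. Empirical standard errors in SD units:

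| Analysis | rho 0.5 | rho 0.7 | rho 0.8 |
|---|---|---|---|
| Change | 0.2548 | 0.2037 | 0.1633 |
| Change + covariates picked by imbalance | 0.2579 | 0.2062 | 0.1656 |
| T0 as covariate | 0.2246 | 0.1881 | 0.1562 |
| T0 + one pre-named prognostic covariate | 0.2208 | 0.1857 | 0.1552 |

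The squared ratios of the third row to the first are 0.78, 0.85 and 0.91, close to the formula. Covariates picked by imbalance did not improve the change contrast.

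The reason is structural. A time-constant characteristic entered as a main effect adds the same amount to a patient's T0 and T1 values, so with complete data it drops out of the T0-T1 difference.

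**Type I error.** Across all four analyses it lay between 4.8% and 5.4%. The Monte Carlo standard error is sqrt(0.05 x 0.95/8000) = 0.24 percentage points, so this is compatible with 5%.

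**How open the covariate set is.** Data collection offers at least nine candidates: age, gender, dementia type, CIRS, incontinence, restraints, medication, other therapies and BANS-S. For 5 to 10 independent candidates, the chance that at least one differs at p < 0.05 is 1 - 0.95^5 = 23% to 1 - 0.95^10 = 40%.

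**The case against.** The strongest defence is that nothing here is invalid. A time-by-group mixed model with T0 as an outcome is unbiased under randomisation and keeps the data of patients who stop early, which the article expressly wants. A condensed article may also leave a common-T0-mean constraint and a covariate list to an analysis plan. This stands in part: silence on the constraint is not an error. But the change contrast and the imbalance-driven rule are both positive statements, and a plan that named covariates regardless of imbalance would replace the rule rather than fill it in.

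Four stronger readings are tempting and are not supported:

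- **That p-values and intervals are not nominal.** Selection on imbalance alone left type I error at about 5%. Inflation would need covariates to be chosen after results were seen, and the article does not say that this will happen. It does not even state a significance test of imbalance.
- **That the baseline is thrown away.** The change contrast uses it. Of the variance reduction that baseline adjustment offers over ignoring T0, change scores capture (1 - 0.60)/(1 - 0.51) = 82% at rho 0.7 and (1 - 0.40)/(1 - 0.36) = 94% at rho 0.8. Only at about 0.5 or below do they gain nothing.
- **That the loss is 25% or more.** This needs rho of 0.5 or less. Each period averages two weeks of continuous recording, which makes a higher correlation more likely.
- **That the loss is serious because the trial is underpowered.** Whether 66 patients suffice turns on other matters, among them the unstated sidedness of alpha. That is a separate question and lends this point no weight.

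**Conclusion.** The point holds as a free improvement, not as a validity error. The contrast that the article reads as the PAS effect is less precise than a baseline-adjusted one for every rho below 1. If two-week averaging puts rho between 0.7 and 0.9, the saving is 15% to 5% of the variance, or 80% power becoming 86% to 82%. At 0.5 it would be 25%, or 90% power. The covariate rule is poor practice because it leaves the model unfixed, but its practical effect on the T0-T1 contrast is small.

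The variance figures assume equal variances and complete data. They also assume that T0 has the same expected value in both arms. Procedure describes randomisation before the baseline fortnight, but both arms sleep on their own beds during it, so the assumption is reasonable for actigraphy. The form of the result is certain; its size depends on a correlation that the article does not give.

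**What to change.** - In the mixed model, keep T0, T1 and T2 as outcomes but constrain the two arms to a common T0 mean. This recovers essentially all of the lost precision and keeps every observation. The alternative is to use the patient's T0 value as a covariate, with T1 and T2 as outcomes.
- Delete the correction for observed differences between the arms. Name a few prognostic covariates in advance from data already collected, for example BANS-S and baseline psychotropic use, and include them whatever imbalance appears. In a model with T0 as an outcome, let their effects differ by period; otherwise they largely cancel from the T0-T1 contrast.
- State this wording before the outcome data are examined.

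The cost is analysis wording only: no new measurements, visits or patients.
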